#### Subgroup analysis

Since the effect of the iCBT program may differ according to specific population, the effect will also be analyzed by subgroups. Participants will be divided according to their initial severity of psychological distress. We will treat high/low psychological distress (i.e., participants who scored 5 or more on K6 at baseline) as one stratification factor and perform subgroup analysis. In addition, newly graduated nurses (i.e., less than 1 year of nursing experience) have been reported to have higher depressive symptoms compared to veteran nurses [7, 69, 70]. We will treat participants with more/less than 1 year of nursing experience as another stratification factor and conduct subgroup analysis.

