### Sample size calculation

This study’s iCBT program will include mental health professionals’ support. Previous meta-analyses of iCBT aimed at improving depressive symptoms among workers, both with or without supports, yielded effect sizes of 0.16–0.25 [19, 20]. Programs with supports have been reported to be more effective compared to self-guided iCBT programs [15, 20]. To detect a small effect size of 0.2 or greater at an alpha error probability of 0.05 and a power (1-β) of 0.80 using G*Power V.3.1.9.2 [67], a sample size of 394 participants per arm would be required. Anticipating a dropout rate of 25%, the necessary sample size would be 525 participants per arm.

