### Randomization

After the baseline survey, eligible participants will be randomly assigned either to the intervention or control group using stratified permuted-block randomization, with a random block size of two. Participants will be stratified based on K6 score (5 or greater or less than 5) at baseline survey and worksite. The intervention effect may differ according to the severity of the psychological distress at baseline. The K6 cut-off score will be based on the optimal cut-off value (i.e., 4/5), which was used to separate patients with mood disorders in a previous study [66]. An independent biostatistics researcher will generate a stratified permuted-block random table. This table will be password-protected and concealed to other researchers. The researcher (KK) will carry out enrollment and another independent researcher will conduct allocation. During the random assignment, only the researcher will be able to access the stratified permuted-block random table.

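### The subgroup analyses are motivated by a possible difference in effect, but the plan names only separate subgroup analyses and no test of that difference

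*Protocol article*

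**What the plan says.** The Subgroup analysis section of the protocol article opens with its reason: "Since the effect of the iCBT program may differ according to specific population, the effect will also be analyzed by subgroups". It then names two factors. The first is baseline psychological distress, with participants divided at a K6 score of 5. The second is nursing experience: "We will treat participants with more/less than 1 year of nursing experience as another stratification factor and conduct subgroup analysis". The Randomization section gives the same kind of reason for using K6 there: "The intervention effect may differ according to the severity of the psychological distress at baseline".

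The only interaction named anywhere is in the Statistical methods section. It is group by time, and it serves as the measure of the intervention effect itself. No term involving a subgroup factor is mentioned.

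The article gives no expected proportion for either factor. The sample size section supplies the design effect and the analysed number: "To detect a small effect size of 0.2 or greater", with "a sample size of 394 participants per arm would be required". The earlier meta-analyses that it cites "yielded effect sizes of 0.16–0.25".

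**The concern.** The reason given is a between-subgroup question: does the effect differ? The method given is a within-subgroup analysis. Applying the group by time test separately in each subgroup yields two answers to whether there is an effect here, and none to whether the two effects differ.

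One subgroup can reach significance and the other miss it when the true effects are identical. This can happen by chance alone when the subgroups are of equal size, and it becomes more likely when one is much smaller, as may be the case for nurses in their first year. At stake is a published claim that the programme helps only distressed nurses, or only experienced ones, when the data show no such thing.

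**Working it through.** **Inputs from the Sample size calculation section.** d = 0.2; alpha 0.05 (sidedness not stated; two-sided reproduces the stated number); power 0.80; 394 analysed per arm; 25% dropout; 525 randomised per arm. Sensitivity range for d: 0.16 to 0.25.

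**Assumed, because the article does not give it.** The split between subgroups: 50:50 down to 5:95.

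**Step 1. Reproduce the plan's figure.** A two-sided two-sample t-test with d = 0.2 and 394 per arm has power 0.8006; with 393 it has 0.7996. So 394 is confirmed. 394 / (1 − 0.25) = 525.3, which agrees with 525.

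**Step 2. Power within a subgroup of n per arm.** Normal approximation: power = Φ(d·√(n/2) − 1.96).

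- 50:50, n = 197: 0.2 × √98.5 = 1.985, and Φ(0.025) = 0.510.
- 10:90, n = 39.4: 0.2 × √19.7 = 0.888, and Φ(−1.072) = 0.142. For n = 354.6: 0.2 × √177.3 = 2.663, and Φ(0.703) = 0.759.

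**Step 3. Probability that exactly one subgroup is significant.** The subgroups are disjoint, so this is p1(1 − p2) + p2(1 − p1). At 50:50 it is 2 × 0.510 × 0.490 = 0.500. With the same true d = 0.2 in both subgroups and 394 per arm:

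| Split | Power, smaller | Power, larger | Exactly one significant |
|---|---|---|---|
| 50:50 | 0.510 | 0.510 | 0.500 |
| 30:70 | 0.336 | 0.651 | 0.549 |
| 20:80 | 0.241 | 0.709 | 0.609 |
| 10:90 | 0.142 | 0.759 | 0.686 |
| 5:95 | 0.091 | 0.781 | 0.730 |

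**Step 4. Sensitivity, over splits from 50:50 to 5:95.**

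- d = 0.16: 0.458 to 0.577.
- d = 0.25: 0.421 to 0.825.
- d = 0.2 with all 525 per arm analysed: 0.466 to 0.801.
- No effect in either subgroup: 2 × 0.05 × 0.95 = 0.095.

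**Step 5. The interaction test under the same conditions.** In 20,000 simulated trials with d = 0.2 in both subgroups, a two-sided 5% test of the difference was significant in 4.7% at 50:50 and 4.9% at 10:90. In the same simulations, exactly one separate test was significant in 50.1% and 68.7%.

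**Step 6. What the interaction test can detect.** Its standard error in units of d is √(2/n1 + 2/n2). At 50:50 this is √(4/197) = 0.1425. Power for a difference in d of 0.2 is Φ(0.2/0.1425 − 1.96) = 0.289. The difference detectable with 80% power is 2.80 × 0.1425 = 0.40. At 10:90 the power is 0.13 and the detectable difference 0.67.

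**The case against.** A reader might infer that the plan will declare a differential effect by comparing subgroup p-values, or that it rules out an interaction test. The article says neither. It is silent on how differences will be judged, it is a condensed account, and model terms for secondary analyses are often set out in a fuller document. Its hypotheses contain no statement about effect modification, and it plans Cohen's d with 95% confidence intervals, so nothing prevents it from reporting subgroup estimates properly. This stands, and it is why the risk is stated as conditional. It does not remove the point, because the article does fix the factors, the cut-offs and the approach, and that approach does not address the reason given for it.

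A reader might also take one half as a fixed error rate whenever the effects are identical. It is not. It requires a real common effect near 0.2 and a fairly even split. It is higher for uneven splits and about 9.5% if the programme does nothing. The calculation also uses simple two-sample tests, and power under the planned repeated-measures model would differ.

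Finally, describing experience as a stratification factor might look like a contradiction, since randomisation is stratified only on K6 and worksite. In its place under Subgroup analysis the phrase most naturally means dividing the sample for analysis, and stratified analysis does not require stratified randomisation. This is a matter of wording only.

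**Conclusion.** The point holds in a limited form: the plan gives possible effect differences as its reason for the subgroup analyses and names no analysis that tests them. If the separate analyses are used for that purpose, a spurious one-group-only result occurs about 50% of the time at d = 0.2 with an even split, and about 69% to 73% with 10:90 to 5:95 splits. Over d from 0.16 to 0.25 and all the splits considered, the range is about 42% to 83%, against about 5% for an interaction test. These figures rest on assumed splits, 394 analysed per arm, a true effect common to both subgroups, and two-sample tests in place of the mixed model. The analyses are secondary, and the conclusion on the primary outcome is unaffected.

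**What to change.** For each factor, fit the full-sample mixed model with the subgroup main effect and its interactions added, including group by time by subgroup. Report the interaction estimate and both subgroup effects with 95% confidence intervals at three and six months (the article does not single out one of these visits as primary). Claim a differential effect only on the interaction.

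The cost is a few model terms per factor and a sentence or two of text, with no change to design, sample size or data collection. The drawback is low power: about 29% for a difference in d of 0.2 at 50:50, and less with uneven splits. The plan should therefore label the subgroup results exploratory and state that a non-significant interaction is not evidence of equal effects. Fewer subgroup claims will be possible.

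Optionally, call experience a subgroup variable, so that stratification refers only to the randomisation.

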### Data monitoring

A data monitoring committee (DMC) will consist of at least one independent member. The trial will be checked by the DMC. After randomizing the participants, the DMC will meet every 3 months to review a report created by the researchers to monitor the progress of recruitment and data collection (e.g., completion rates for each follow-up).

### Data confidentiality

After the surveys, the collected data will be transferred to a password-locked stand-alone PC. The PC will be kept in a locked research room at the Department of Psychiatric Nursing in the Graduate School of Medicine at the University of Tokyo. The collected data will be saved as linkable anonymous data with sequentially allocated numbers. The researchers will be able to access the data.

### Dissemination of research findings

The findings of this study will be published in peer-reviewed international journals. We will also present the results and findings at related research conferences, academic symposiums, and seminars.

## Discussion

The greatest strength of this study is that it is the first RCT, to the best of our knowledge, to evaluate the effect of an iCBT program on improving depressive symptoms among nurses. If successful, the iCBT program for nurses could be a promising tool to improve depressive symptoms as a primary prevention. Additionally, this study also aims to add to the evidence on the effect of iCBT programs on positive health outcomes (i.e., work engagement and work performance) among nurses.

Nevertheless, this study has some limitations. All data, including MDE measurement, will be measured by self-report, which may be affected by situational factors at work and participants’ perceptions. In addition, due to limited resources and funding, the participants will not be able to submit their homework via smartphone, which may limit the effect of our intervention program. Moreover, there is the possibility that participants in the control group will obtain information about the iCBT program from participants in the intervention group in the same ward or workplace. This contamination may weaken the intervention effect.

## Data Availability

Those interested in this study will communicate all outcomes and findings through publications.

## Abbreviations

BA: behavioral activation
BDI-II: Beck Depression Inventory-II
CB: cognitive behavioral
CBT: cognitive behavioral therapy
CI: confidence interval
DMC: data monitoring committee
DSM-IV-TR: DSM, Fourth Edition, Text Revision
EAP: Employee Assistance Program
HPQ: WHO Health and Work Performance Questionnaire
iCBT: Internet-based cognitive behavioral therapy
JCQ: Job Content Questionnaire
MDE: major depressive episode
NNT: Number Needed to Treat
RCT: randomized controlled trial
SMD: standardized mean difference
SPIRIT: Standard Protocol Items: Recommendations for Interventional Trials
TAU: treatment as usual
UMIN: University Hospital Medical Information Network
UMIN-CTR: University Hospital Medical Information Network clinical trial registry
UWES: Utrecht Work Engagement Scale
WHO-CIDI: WHO-Composite International Diagnostic Interview
